## Abstract

**Background:**

HIV case-finding and linkage to care are critical for control of HIV transmission. In Kenya, >50% of seropositive individuals are unaware of their status. Assisted partner notification is a public health strategy that provides HIV testing to individuals with sexual exposure to HIV and are at risk of infection and disease. This parallel, cluster-randomized controlled trial will evaluate the effectiveness, cost-effectiveness, and feasibility of implementing HIV assisted partner notification services at HIV testing sites (clusters) in Kenya.

**Methods/design:**

Eighteen sites were selected among health facilities in Kenya with well-established, high-volume HIV testing programs, to reflect diverse communities and health-care settings. Restricted randomization was used to balance site characteristics between study arms (*n* = 9 per arm). Sixty individuals testing HIV positive (‘index partners’) will be enrolled per site (inclusion criteria: ≥18 years, positive HIV test at a study site, willing to disclose sexual partners, and never enrolled for HIV care; exclusion criteria: pregnancy or high risk of intimate partner violence). Index partners provide names and contact information for all sexual partners in the past 3 years. At intervention sites, study staff immediately contact sexual partners to notify them of exposure, offer HIV testing, and link to care if HIV seropositive. At control sites, passive partner referral is performed according to national guidelines, and assisted partner notification is delayed by 6 weeks. Primary outcomes, assessed 6 weeks after index partner enrollment and analyzed at the cluster level, are the number of partners accepting HIV testing and number of HIV infections diagnosed and linked to care per index partner. Secondary outcomes are the incremental cost-effectiveness of partner notification and the costs of identifying >1 partner per index case. Participants are closely monitored for adverse outcomes, particularly intimate partner violence. The study is unblinded due to practical limitations.

**Discussion:**

This rigorously designed trial will inform policy decisions regarding implementation of HIV partner notification services in Kenya, with possible application to other parts of sub-Saharan Africa. Examination of effectiveness and cost-effectiveness in diverse settings will enable targeted application and define best practices.

**Trial registration:**

ClinicalTrials.gov NCT01616420.

## Background

HIV testing is central to HIV control. Knowledge of serostatus promotes safer sexual practices in a variety of populations [1-4] and is an essential first step in the uptake of HIV treatment, which improves survival and reduces HIV transmission [5]. However, despite increased awareness of HIV and improved availability of anti-retroviral therapy (ART), an estimated 60% of infected individuals in sub-Saharan Africa are unaware of their status [6].

Assisted partner notification services (APS) is a public health strategy used to curb the spread of sexually transmitted infections (STIs) by testing and treating the sexual partners of infected index cases. The intervention typically involves a public health worker interviewing persons diagnosed with an STI (i.e., index cases) about their sexual partner(s) and then providing the index case with some level of assistance notifying their partners and assuring their testing. Some health departments in the US and Europe developed APS programs for HIV as early as the 1980s, and APS has been found to increase HIV case-finding and safer behaviors [7]. Despite its resource-intensiveness, some studies suggest that APS can be cost-effective and even cost-saving due to the potential to prevent HIV transmission and the resulting costs of HIV care [8]. APS programs incorporate confidentiality safeguards and intimate partner violence (IPV) screening, and harms are rarely reported [7]. CDC guidelines now recommend APS integration into all HIV control programs [9].

US and European data supporting APS for HIV control must be cautiously applied to HIV-endemic regions. Differences in culture, socioeconomic conditions, health systems, background levels of HIV testing, the status of youth and women, and perceptions of HIV infection may all affect the feasibility and effectiveness of APS. Two recent reports from sub-Saharan Africa show promising results. An HIV APS program in Cameroon diagnosed one new case of HIV for every 3.2 index cases interviewed [10]. In a small (*n* = 245) randomized controlled trial at STI clinics in Malawi, APS doubled the number of sexual partners testing for HIV compared to usual practices, and >50% of these partners were HIV seropositive [11]. In both reports, APS was acceptable and safe. While these studies provide preliminary evidence that HIV APS can be productively implemented in sub-Saharan Africa, replication in large, well-designed trials is required before this strategy is widely adopted.

Kenya has an HIV prevalence of 5.6%. Despite major national initiatives to improve HIV testing, 53% of HIV-seropositive individuals are unaware of their status [12], and most perceive themselves to be at low or no risk [13]. Currently, there is no HIV APS in Kenya; the standard of care is passive referral, in which individuals testing HIV-seropositive are encouraged to disclose their status to their partners and bring them for testing. HIV APS has the potential to improve HIV control in Kenya by identifying those at risk and facilitating both testing and linkage to care. Kenya’s strong HIV research infrastructure provides the opportunity to answer relevant questions about scale-up by rigorously evaluating HIV APS. These factors brought the Kenyan Ministry of Health’s National AIDS and STI Control Programme (NASCOP), Kenyatta National Hospital (KNH), and the University of Washington together to conduct a cluster-randomized trial at HIV testing sites in Kenya to evaluate the effectiveness, cost-effectiveness, and feasibility of HIV APS across a variety of settings.

The primary objective of the study is to evaluate the effectiveness of HIV APS in Kenya for HIV case-finding and linkage to care among sexual partners of index cases. We hypothesize that APS will increase HIV testing, new HIV diagnoses, and linkage to care among HIV-positive partners compared to passive referral, and that case-finding will be enhanced by extending APS beyond the primary partner to other sexual partners. We also predict that HIV APS will be acceptable with minimal social harms, and that APS will be cost-effective from both payer and societal perspectives. A cluster-randomized design was selected to minimize risk of contamination between arms and to evaluate barriers in implementation and program costs at the facility level. Outcomes will be analyzed at the cluster level. Examining challenges and outcomes across diverse study sites will provide insights into best practices to help guide APS implementation.

## Methods

### Study design

This study is a multicenter, parallel, cluster-randomized controlled trial. In brief, 18 HIV testing sites in Kenya (clusters) were selected based on both practical and theoretical considerations and allocated to intervention and control arms (*n* = 9 clusters per arm) using a restricted randomization process (details below). In the intervention arm, APS is implemented immediately after index enrollment; in the control arm, APS is delayed for 6 weeks after index enrollment. Care provided in the control arm during the first 6 weeks of randomization is consistent with the current standard of care in Kenya (i.e., passive referral with no specialized partner services). Delayed provision of APS to the control arm allows for evaluation of additional study outcomes (i.e., partners notified and tested via APS >6 weeks after study enrollment), as well as providing these partners the opportunity for HIV testing. Sites enroll participants in a staggered fashion to ensure adequate time for individual site preparation and staff training, as well as oversight of study activities.

### Study sites

Eighteen HIV testing and counselling (HTC) sites in Kenya were selected as study sites (clusters). HTC in Kenya is carried out in a variety of settings by counsellors trained according to NASCOP guidelines [14]. Approaches include voluntary counselling and testing (VCT), provider-initiated testing and counselling (PITC), home-based testing, mobile testing, and antenatal testing. Treatment is provided by multidisciplinary teams at comprehensive care centers (CCC). This includes medical evaluation and management; laboratory monitoring; provision of antiretroviral treatment (ART) and co-trimoxazole; nutritional, adherence, and prevention counselling; and psychosocial support services [15].

Study sites were selected to reflect the diverse communities and health-care settings in Kenya in order to increase generalizability of results and to gain insights into implementing APS in different environments. As the first step in site selection, NASCOP identified >30 sites with well-defined VCT and/or PITC programs and moderate to high volume of HIV testing to facilitate timely completion of the study. Sites were then selected from this list to ensure diversity in terms of the following: geographical location within Kenya and by extension sociocultural practices; proximity to a city (urban, peri-urban, and rural); HIV prevalence; and health-care facility level. Principal investigators and study coordinators conducted site visits to obtain further details (e.g., the populations served, existing HTC and CCC services, space, rate of HIV case-finding). Based on these factors and consent for participation from facility leadership, they enrolled the final 18 sites (Figure 1).

**Figure 1 Fig1:**
[figure not shown]
**Distribution of APS study sites in Kenya.** The 18 HIV testing and counselling (HTC) sites participating in the APS study are shown on a map of Kenya, with estimated HIV prevalence among adults for each county [16]. A star (*) indicates that the site was assigned to the intervention (immediate APS) arm. U, urban; P, peri-urban; R, rural.

### Randomization

A restricted randomization process was used for site (cluster) allocation to intervention and control arms (Figure 2). To ensure balance between study arms in terms of key site characteristics, sites were categorized based on county (Nairobi, Kiambu, Murang’a, Kisumu) and proximity to a city (urban, peri-urban, rural). Within each sub-group, all possible randomizations that evenly distributed the sites into two study arms were generated using Excel; e.g., there were 70 ways to randomize the eight urban Nairobi county sites to four sites per arm. Since there were three peri-urban sites in Kisumu, they were randomized to two sites to one arm and one site to the other arm, and the Murang’a site was grouped with the single Kisumu site. These sub-group randomizations were then combined in all possible ways to distribute nine sites into each arm (*n* = 3,360), and one combination was selected using a random number generator.

**Figure 2 Fig2:**
[figure not shown]
**Restricted cluster randomization of sites in APS study.** To ensure balance between study arms for key site characteristics, the 18 sites (clusters) were categorized by county and proximity to an urban area. Randomization was performed for each sub-group, and all possible combinations of these randomizations were generated. One combination was then selected using a random number generator. Note: the star (*) indicates that the three Kisumu peri-urban sites were randomized to two in one arm and one in the other; the Murang’a site then occupied the unfilled spot.

Randomization and allocation were performed at the University of Washington (USA) by the study statistician, who had no knowledge of the sites other than the characteristics used for categorization. Cluster allocation was not concealed from the sites or study staff. To minimize bias, randomization was performed after enrollment of all clusters and prior to any individual enrollment.

Table 1 shows the baseline characteristics of the study sites. Distribution of geographic location and proximity to urban areas was comparable between study arms as a result of restricted randomization. Quantitative variables of interest—total and positive HIV tests per month, gender of clients, balance between VCT and PITC testing, and percent of clients testing positive—were similarly distributed in each study arm, with no significant differences by Mann–Whitney U test. Unfortunately, data on baseline rates of linkage to care are not routinely collected. Most of the selected facilities follow up with clients regarding linkage to care in some manner (by phone or home visits), and all have a CCC on site. The KNH VCT site also employs peer mentors (HIV-positive individuals enrolled in care) to improve linkage to care for newly diagnosed clients; no other sites routinely employed peer mentors or other strategies.

**Table 1 Tab1:** **Baseline characteristics of APS study sites based on 2012 data.**
^**a**^

**Study arm**	**Study sites**	**County**	**Urban vs ** **rural**	**Facility funding source**	**Health facility level** ^**b**^	**Number of HTC staff**	**Number of HIV tests per month**	**Females among those tested (%)**	**Type of HTC used (%)**	**Number of positive HIV tests per month**	**Positive among tested (%)**	**Females among positive tests (%)**	**Start date at site**
Intervention: immediate APS	Kariobangi Health Centre	Nairobi	Urban	Nairobi City Council	2	2	170	61.1	VCT: 89.8	24	14.2	67.6	October 2013
									PITC: 10.2				
	BabaDogo VCT Centre	Nairobi	Urban	Nairobi City Council	2	2	212	46.4	VCT: 78.8	27	12.9	58.2	April 2014
									PITC: 21.2				
	STC Casino	Nairobi	Urban	Nairobi City Council	2	1	439	53.1	VCT: 51.1	43	9.9	55.9	July 2014
									PITC: 48.9				
	Mama Lucy Kibaki Hospital	Nairobi	Urban	Public	3	2	263	64.7	VCT: 64.1	38	14.3	64.0	July 2014
									PITC: 35.9				
	Karuri Health Centre	Kiambu	Peri-urban	Public	2	1	287	60.9	VCT: 75.3	13	4.5	61.3	June 2014
									PITC: 24.7				
	JOOTRH-Russia	Kisumu	Urban	Public	3	2	2,262	69.4	VCT: 2.4	134	5.9	68.8	August 2013
									PITC: 97.6				
	Maseno Mission Hospital	Kisumu	Peri-urban	Private	3	2	79	54.8	VCT: 40.5	6	7.7	58.9	March 2014
									PITC: 59.5				
	Chulaimbo Sub-District Hospital	Kisumu	Peri-urban	Public	3	3	551	55.2	VCT: 44.4	71	12.9	58.5	June 2014
									PITC: 55.6				
	Ongi’elo Health Centre	Siaya	Rural	Public	2	3	199	38.7	VCT: 28.2	15	7.6	59.7	June 2014
									PITC: 71.8				
Control: delayed arm	Kenyatta National Hospital	Nairobi	Urban	Public	4	7	3,942	60.3	VCT: 26.3	218	5.5	62.3	August 2013
									PITC: 73.7				
	Mbagathi District Hospital	Nairobi	Urban	Public	3	9	919	56.5	VCT: 13.4	106	11.6	55.4	November 2013
									PITC: 86.6				
	Huruma Lions Dispensary (NCC)	Nairobi	Urban	Nairobi City Council	2	1	435	76.7	VCT: 72.1	33	7.6	82.1	July 2014
									PITC: 27.9				
	Pumwani Maternity VCT Centre	Nairobi	Urban	Nairobi City Council	3	4	389	64.0	VCT: 100	16	4.1	65.8	July 2014
									PITC: 0				
	Kiambu District Hospital	Kiambu	Peri-urban	Public	3	2	778	55.0	VCT: 34.1	82	10.5	60.1	November 2013
									PITC: 65.9				
	Kirwara Sub-District Hospital	Murang’a	Peri-urban	Public	3	1	59	57.0	VCT: 18.3	3	5.0	65.7	June 2014
									PITC: 81.7				
	Kisumu District Hospital	Kisumu	Urban	Public	3	8	990	60.5	VCT: 23.1	129	13.1	58.9	November 2013
									PITC: 76.9				
	Kombewa District Hospital	Kisumu	Peri-urban	Public	3	4	293	52.9	VCT: 55.0	37	12.5	53.5	April 2014
									PITC: 45.0				
	Abidha Health Centre	Siaya	Rural	Public	2	2	141	67.4	VCT: 4.5	13	9.1	60.1	May 2014
									PITC: 95.5				

*Abbreviations*: *APS* assisted partner notification services, *HTC* HIV testing and counselling, *NASCOP* National AIDS and STI Control Programme, *PITC* provider-initiated testing and counselling, *VCT* voluntary testing and counselling.

^a^Data from the 2012 calendar year provided by the NASCOP Strategic Information Management Unit.

^b^Health-care facilities in Kenya are categorized into four levels: 1, community level; 2, sub-district facility; 3, district hospital; and 4, national hospital.

### Study procedures

#### Staff recruitment and training

We recruited NASCOP-certified HTC counselors with research experience to serve as APS study staff, henceforth referred to as ‘health advisors.’ Staff were trained and supported to provide high-quality APS by adapting training materials developed by the Cameroon Baptist Christian Health Board [10] to the Kenyan setting. Topics included are as follows: study procedures, client flow, informed consent processes, participant eligibility, notification of partners, IPV monitoring, data entry on smartphones, clinical training on HIV/AIDS staging, treatment and management, and diagnosis of opportunistic infections and sexually transmitted infections according to the Kenyan national guidelines. Refresher training sessions are conducted regularly, including updates on the new HTC algorithm introduced in 2013 by NASCOP [14].

#### Participants: inclusion/exclusion criteria

Inclusion criteria for index participants are defined as follows: 1) 18 years or older; 2) able to give informed consent; 3) HIV-seropositive test result at one of the study sites; 4) not enrolled in HIV care; and 5) willing to provide information on at least one sex partner from the preceding 3 years. Exclusion criteria are pregnancy (by self-report) and/or high risk for IPV due to safety concerns (described below). Partners are considered eligible for the study if 18 years or older and able to give informed consent.

#### Index participant enrollment

At study sites, clients are tested and counselled by resident HTC counsellors according to national HTC guidelines. At both intervention and control sites, all clients testing HIV-seropositive are informed about the APS study by the HTC counsellors (who are not employed by the study). If interested, clients are referred to health advisors for screening. Following a screening informed consent process, clients are screened for eligibility as an index participant. If eligible and willing to participate, written consent for study participation is obtained, and participants are informed whether they are in the immediate or delayed randomization arm.

Health advisors then administer questionnaires on demographic characteristics, sexual behavior, HIV testing history, and HIV care and treatment status. These questionnaires seek to elicit the following information on each of an index participant’s sexual partners from the prior 3 years: home/work addresses and contact information, index patient’s relationship to the partner (i.e., spouse, girlfriend or boyfriend, casual contact), and knowledge of the partner’s HIV status. Index participants are assigned unique identification numbers, and each partner is assigned a linked identification number.

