#### Blinding

This study was carried out in an unblinded fashion. Blinding of study staff and participants was not feasible given the distinct protocols and timelines of the two study arms, including procedures for assessment of outcomes.

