### Outcome measures

Outcomes will be compared between intervention and control arms based on data collected 6 weeks after enrollment of index participants and will be analyzed at the cluster level.

Primary outcomes are as follows: 1) HIV testing of partners (number of partners of an index participant that were tested for HIV, offset by the number of partners with locator information provided by the index participant); 2) newly identified HIV-infected partners (number of partners of an index participant identified as HIV-infected, offset by the number of partners of that index participant who were HIV tested); and 3) linkage to HIV care (number of partners of an index participant who were linked to HIV care, offset by the number of partners of an index participant identified as HIV-infected; analysis will be limited to index participants with at least one HIV-infected partner).

Secondary outcomes are as follows: 1) the incremental cost per HIV-infected person identified and linked to care, including ART, and the incremental cost-effectiveness per incident HIV infection, HIV-related death, and disability adjusted life-year (DALY) averted in Kenya from payer and societal perspectives; and 2) costs of identifying >1 partner per index case.

There have been no changes to outcome measures.

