In terms of study execution, we have found that health advisor personalities and training are critical for the success of APS. Previous reports have found that individuals decline HIV APS due to shock and shame about HIV diagnosis, mistrust of public health services, and fear of notifying partners [11,26]. APS study health advisors were selected based on experience as effective HCT counselors and received additional training on how to build rapport, assure confidentiality, and convey potential benefits for index participants and partners. Health advisors report that index participants often name only one partner but may reveal additional partners after tactful probing. As we hypothesize that tracing multiple partners will increase HIV case-finding, health advisors are encouraged to share non-judgmental approaches to enhance disclosure of multiple partners, while respecting autonomy. Such approaches would be important to incorporate into an APS program. We are also planning a qualitative study to explore why individuals in Kenya may decline to participate in APS and how such barriers may be overcome.

Challenges have arisen during the partner notification process. Initially, partners may be resistant to communication with health advisors due to suspicions about the identity of the caller (e.g., prank caller, debt collectors). These concerns are usually assuaged by producing proof of identification and affiliation with the Ministry of Health-NASCOP and KNH. As described, the script for partner notification was modified early in the study to avoid partners demanding to know who provided their information; this has improved acceptance. Another challenge for health advisors is verbal abuse from partners during phone calls. Though they have never encountered physical violence, staff are expected to follow safety precautions such as travelling in pairs to risky or remote areas. Finally, enrollment of notified partners has been difficult at some sites. Success likely depends on the approach of health advisors, partner populations, and the interaction between them. Exploring how effectiveness varies by site characteristics and health advisor may highlight best practices.

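### The offset of primary outcome 1 is collected after index participants learn their arm and by unblinded staff, so it can differ by arm; protect the elicitation step and align the outcome with the powered scale

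*Protocol article*

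**What the plan says.** The order of steps is set out under Index participant enrollment in the protocol article. Eligibility screening and written consent come first, and at that point "participants are informed whether they are in the immediate or delayed randomization arm". Next, "Health advisors then administer questionnaires on demographic characteristics, sexual behavior, HIV testing history, and HIV care and treatment status". For each partner in the past 3 years these questionnaires collect, among other items, "home/work addresses and contact information, index patient’s relationship to the partner".

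Under Outcome measures, primary outcome 1 is the number of an index participant's partners who were tested, "offset by the number of partners with locator information provided by the index participant". The denominator is therefore the product of that interview.

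Staff are not shielded from the arm. Under Randomization: "Cluster allocation was not concealed from the sites or study staff". Under Blinding: "Blinding of study staff and participants was not feasible given the distinct protocols and timelines of the two study arms". The Discussion reports that "index participants often name only one partner but may reveal additional partners after tactful probing" and that health advisors are encouraged to bring this about.

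Two other places use a different scale. The abstract describes the outcome as the "number of partners accepting HIV testing" and counts per index partner, and the power calculation models partners tested per index case.

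**The concern.** An offset works as a neutral denominator only if allocation does not affect it. Here it is a post-allocation quantity, and the article itself suggests two ways in which it could move.

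- **Participant side.** Someone just told that staff will approach partners within 1–2 weeks may hold back a second partner or a phone number. Someone told that contact is 6 weeks away may have less reason to. The Discussion cites fear of notifying partners as a known reason for declining these services.
- **Staff side.** Health advisors know the site's arm, and how hard they probe affects how many partners are named.

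The first would shrink the immediate-arm denominator and raise the ratio. The second could enlarge it and lower the ratio. Either could create or mask a difference in the powered comparison without any change in the number of partners tested. The limitations section gives tracing intensity and encouragement to test as examples of bias from lack of blinding, but not partner elicitation.

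**Working it through.** **1. The plan's own figure.** Inputs from Sample size and power analysis: 0.1 partners tested per index in the delayed arm, twofold effect (so 0.2), 60 index cases per site, k = 0.25, two-sided 5%, power 80%. The Hayes–Moulton formula for rates is

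c = a + (1.96 + 0.84)² × [(0.1 + 0.2)/60 + 0.25² × (0.1² + 0.2²)] / (0.2 − 0.1)².

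The bracket is 0.005 + 0.003125 = 0.008125, and the second term is 6.38. With a = 1, c = 7.38, or 8 sites per arm. With a = 2 (the matched or stratified variant), c = 8.38, or the stated 9. The sample size is therefore not in question. What matters is that the trial was powered on tests per index, not on tests per located partner.

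**2. The ratio.** Let T be partners tested per index and M partners with locator information per index. Then

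offset ratio = (T_imm/M_imm) / (T_del/M_del), and per-index ratio = T_imm/T_del.

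The article gives no value for M, so the values below are assumptions.

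**3. Assumption A: naming changes M but not T.** T = 0.10 in both arms and M_del = 1.5.
- M_imm = 1.2: (0.10/1.2)/(0.10/1.5) = 1.25.
- M_imm = 1.8: (0.10/1.8)/(0.10/1.5) = 0.83.
- The per-index ratio is 1.00 in both cases, because A fixes it there.

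**4. Assumption B: every located partner is equally likely to test.** The probability is 0.10/1.5 = 0.067. With M_imm = 1.2, T_imm = 1.2 × 0.067 = 0.08.
- Offset ratio: (0.08/1.2)/(0.10/1.5) = 1.00.
- Per-index ratio: 0.08/0.10 = 0.80.

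**5. Halfway between A and B.** For M_imm = 1.2, T_imm is midway between 0.10 and 0.08, that is 0.09. The offset ratio is (0.09/1.2)/(0.10/1.5) = 1.125 and the per-index ratio is 0.90. Both scales move.

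**6. Effect on error rates, under A only.** The simulation used 9 sites of 60 per arm, gamma–Poisson counts with k = 0.25, a t-test on site rates and 20,000 runs. The planned analysis is GEE, so the results are indicative.
- No effect, M = 1.5 delayed and 1.2 immediate: the offset analysis rejects in 0.14 of runs and the per-index analysis in 0.05.
- True doubling per index, M = 1.2 delayed and 1.5 immediate: the offset ratio falls to 1.60 with power 0.59, against 0.90 per index.

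**The case against.** The strongest reply is that step 3 assumes its result. Partner testing is ascertained at partners' study visits, and partners are reached through the details the index gives. A partner never named is normally not counted as tested, so withholding lowers the numerator too. Step 4 shows the consequence: the offset then removes the distortion and the per-index count carries it. This stands. A reader might infer from step 3 that the per-index scale is immune to differential naming; the documents do not support that.

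Several features also limit the size. Willingness to give information on at least one partner is an eligibility criterion, screened before the arm is disclosed. Staff contact partners in both arms, and only the timing differs. The article describes one set of pre-programmed questionnaires and one staff training, with no difference by arm. The two mechanisms push in opposite directions. All of this stands, and it confines the problem mainly to second and later partners and to completeness of contact details. It does not remove it: a shared questionnaire does not equalise probing by staff who know the arm.

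An offset by located partners is also a legitimate estimand, and the limitations section's examples of unblinded bias are not meant to be exhaustive. Both points are fair. But the chosen denominator is open to allocation, and it is not the scale on which the abstract and the power calculation rest. That mismatch is not itself evidence of naming bias, but it bears on the remedy.

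**Conclusion.** The point holds as a design weakness that should be corrected. The order of steps, the unblinded elicitation and the use of the resulting count as the offset are all in the text, and nothing in the article protects that count from the arm.

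The size and direction are unknown. Under the assumed counts, the offset ratio with no real effect lies anywhere from 0.83 to 1.25 if tests per index are unaffected by naming. It is 1.00, with a per-index ratio of 0.80, if 1.2 rather than 1.5 partners are located and each is equally likely to test. Neither scale is fully robust, so the first thing to protect is the elicitation step itself.

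A reader might also infer that the primary comparison has been biased, or that the offset is a mistake. The documents support neither: they report no partners named by arm, and they show only that the bias is possible.

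**What to change.** 1. For remaining enrolment, complete and lock the partner list after consent and before the participant is told the arm, using the same elicitation script in both arms. This removes the participant-side mechanism, provided the arm has not already been revealed at referral. Staff still know the arm, so the script only reduces differential probing.
2. Bring Outcome measures into line with the abstract and the power calculation: make partners tested per index participant the primary analysis of outcome 1, and keep the rate per located partner as secondary.
3. Compare partners named, and partners with locator information, per index by arm. If these are similar, the two scales should agree. If they differ, neither result should be read alone.

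Cost: no extra visits or staff. Trial status says the intervention had reached all 18 sites with data collection ongoing, so reordering helps only later participants and creates a before/after split in the elicitation procedure that must be recorded. Changing the primary scale in an unblinded trial needs a documented amendment, made before outcomes are compared by arm.
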